### 2.2. Recruitment of Women

The midwives who collaborate in the research will invite pregnant women who attend obstetrics and gynecology consultations for pregnancy control and monitoring and who will give birth to their children in public hospitals in the Servizo Galego de Saúde (Spain) to participate in the study. Subsequently, the personnel in charge of the research will contact the women by telephone and again inform them verbally and in writing about the objective and methodology of the study. Once the consent form has been signed, the different questionnaires will be sent electronically. A questionnaire regarding sociodemographic variables (e.g., age, marital status, education level, employment status and personal monthly income), obstetric history and current pregnancy (e.g., number of previous pregnancies, planned pregnancy, complications) will be developed for this study.

After completion of the baseline questionnaire, participants will be randomly assigned to either the intervention or control group using block randomization, in a 2:1 ratio, using an online randomization program. Study personnel are unaware of which treatment group each participant will be assigned to at the time of the baseline assessment.

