### 2.3. Outcomes and Allocation of Participants to Trial Groups

#### 2.3.1. Primary Outcome

The primary outcome measure will be the difference in the mean anxiety scores between the intervention and control groups assessed by the EDS-3A, STAI and GAD-7 questionnaire before and at the end of the intervention, and one month, 3 months and 6 months after the intervention. Generalized anxiety disorder (GAD) will also be evaluated through the DSM-5 clinical interview at the same time points. In this case, the percentages found will be compared.

The Edinburgh Depression Scale-Anxiety Subscale (EDS-3A) is the anxiety subscale of the Edinburgh Postnatal Depression Scale (EPDS) [42]. Different studies, e.g., [43,44] have found that three items (3, 4, 5) can detect anxiety in women during the perinatal period. Each of the three items has four response options (0 = none, 1 = somewhat, 2 = quite a bit, and 3 = a lot). The total score of the subscale ranges from 0 to 9. The cut-off point used in the EDS-3A to detect anxious symptomatology will be ≥5 [45].

The State–Trait Anxiety Inventory (STAI) [46] assesses both the current level of anxiety and the individual’s predisposition to suffering from anxiety. It consists of 40 items, 20 of which refer to the state subscale (STAI-E), with the other 20 referring to the trait subscale (STAI-R). The score for each subscale ranges from 0 to 60, with higher scores indicating higher levels of anxiety. In this case, the State Anxiety Subscale (STAI-E) will be applied; the recommended cut-off point for women is greater than 31 (75th percentile).

Generalized Anxiety Disorder Screener (GAD-7) [47] is a self-administered instrument consisting of seven items with four response options. The total score ranges from 0 to 21, with the highest scores being the most severe. The GAD-7 has been validated for use in Spanish-speaking pregnant women [48]. The cut-off point used to detect anxiety symptoms will be ≥7 [49].

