The SCID [50] is a semi-structured interview that determines formal diagnosis according to the Diagnostic and Statistical Manual of Mental Disorders (DSM-5). To diagnose generalized anxiety, you need to have had anxiety on most days in the last 6 months in at least three contexts of your daily life and show three of the six anxiety symptoms that are described in the manual. The use of such interviews improves diagnostic reliability by standardizing the assessment process and increases diagnostic validity by facilitating the application of DSM diagnostic criteria and the systematic enquiry for symptoms that might otherwise go unnoticed.

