### 2.8. Analysis Plan

The primary analysis will compare the mean scores of EDS-3A, STAI-E and GAD-7 between the two groups before and after the intervention and one month, 3 months and 6 months after the end of the intervention to evaluate the effectiveness of the protocol in preventing anxiety symptoms. Similar analyses will be performed for the secondary result on depressive symptomatology. For the GAD, the frequencies in the two groups will be compared at the same evaluation periods.

Regarding the effectiveness of treatment, descriptive statistics will be calculated for all questionnaires. Variance analyses for repeated measurements will be performed to compare the differences between each initial score obtained with the different administered questionnaires and the scores at T1 (end of treatment), T2 (after 1 month), T3 (after 3 months) and T4 (after 6 months) will be evaluated. Bonferroni post hoc comparisons will also be conducted. The number of evaluations compared will need to be taken into account to adjust the *p*-value in the Bonferroni test with the aim of minimizing type 1 errors. The treatment effect will be calculated using Cohen’s d for each of the follow-up times. The Reliable Change Index will be calculated for each time in order to determine any significant clinical changes occurring in each individual case post-treatment. To compare differences in GAD, the chi-square test and Fisher’s exact test will be used in the contrast of 2 × 2 tables. In addition, Cochran’s Q test will be used to determine the existence of differences across time points and McNemar’s test will be used to compare the differences in categorical variables between time points in a paired manner.

Data will be analyzed using the Statistical Package for Social Science (SPSS) for Windows version 23.0.

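### The planned between-arm GAD test is valid but leaves out baseline GAD status; stratifying by it costs little, and the gain depends on how common and persistent GAD is

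*Protocol article*

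**What the plan says.** Section 2.3.1 makes the diagnosis a measured outcome beside the questionnaire scores: "Generalized anxiety disorder (GAD) will also be evaluated through the DSM-5 clinical interview at the same time points". The list it refers back to is "before and at the end of the intervention, and one month, 3 months and 6 months after the intervention", so a baseline diagnosis is collected. (The abstract lists only post-baseline points for the interview; sections 2.3.1 and 2.8 include the earlier one.)

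Section 2.8 then fixes the methods:
- Between arms: "For the GAD, the frequencies in the two groups will be compared at the same evaluation periods". The tests are named further on: "To compare differences in GAD, the chi-square test and Fisher’s exact test will be used in the contrast of 2 × 2 tables".
- Over all time points together: "Cochran’s Q test will be used to determine the existence of differences across time points".
- For pairs of time points, the plan adds this: "McNemar’s test will be used to compare the differences in categorical variables between time points in a paired manner".

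Section 2.2 allocates women "using block randomization, in a 2:1 ratio, using an online randomization program" and names no strata. Section 2.4 does not exclude women with GAD at entry, and section 3.1 describes a universal programme.

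**The concern.** A woman's diagnosis before treatment is likely to predict her diagnosis afterwards. The criterion in section 2.3.1 says "you need to have had anxiety on most days in the last 6 months", so an early follow-up interview looks back partly over time before treatment. The 2 × 2 table of arm by follow-up GAD ignores this and counts a pre-existing case the same as a new one, although the stated aim is prevention.

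The two tests that use a woman's earlier diagnosis have no arm term. The baseline 2 × 2 table implied by comparing frequencies at every evaluation period does not adjust any later comparison. The questionnaire scores, by contrast, get a repeated-measures analysis that includes the initial score.

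Two things are at stake. Power is lost when baseline status is prognostic. And with about 47 controls, a chance difference of a few baseline cases passes straight into the follow-up table, where it can look like prevention or hide it.

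**Working it through.** **The plan's own figure.** The only sample size is for a score difference of d = 0.55 with two-sided α = 0.05 and 80% power: n = 2(1.96 + 0.84)²/0.55² ≈ 52 per group, or 53 with the t distribution. This matches the stated 53. No power is stated for GAD, so there is no GAD figure to reproduce.

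**Inputs from the protocol.** 140 women at 2:1 gives 140 × 2/3 ≈ 93 and 47. The wait before the intervention is 4–6 weeks. The seventh weekly session, where the post-treatment assessment is made, comes 6 weeks after the first. T1 is therefore 10–12 weeks after baseline.

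**Overlap of the look-back windows**, taking 6 months as 26 weeks:
- T1: 26 − 12 to 26 − 10 = 14–16 weeks of overlap.
- T3, about 13 weeks after T1 and so 23–25 weeks after baseline: 1–3 weeks.
- T4, about 36–38 weeks after baseline: none.

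**Assumptions not in the protocol.** 80 + 40 analysed; GAD frequency p, equal at baseline and in controls at follow-up; correlation ρ between the two. The range 16.8–19.5% is borrowed from the introduction's figure for anxiety in pregnancy in Spain. The values 3%, 5% and 8% are added because an interview diagnosis may be rarer. Control risk at follow-up is p + ρ(1 − p) after baseline GAD and p(1 − ρ) otherwise. For p = 0.168 and ρ = 0.5 these are 0.168 + 0.5 × 0.832 = 0.584 and 0.168 × 0.5 = 0.084.

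**Power**, simulated with 40,000 trials per setting, two-sided 5%, uncorrected chi-square against Mantel-Haenszel stratified by baseline GAD:

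| GAD frequency | Risk ratio | ρ | Chi-square | Stratified |
|---|---|---|---|---|
| 16.8% | 0.33, all women | 0.5 | 50% | 56% |
| 16.8% | 0.33, all women | 0.7 | 50% | 63% |
| 19.5% | 0.33, all women | 0.5 | 57% | 63% |
| 19.5% | 0.33, all women | 0.7 | 57% | 70% |
| 8% | 0.33, all women | 0.5 | 28% | 30% |
| 8% | 0.33, all women | 0.7 | 28% | 33% |
| 5% | 0.33, all women | 0.5 | 22% | 20% |
| 3% | 0.33, all women | 0.5 | 17% | 12% |
| 16.8% | 0.5, all women | 0.5 | 28% | 32% |
| 16.8% | 1 in baseline cases, 0.33 in others | 0.5 | 12% | 16% |
| 16.8% | 1 in baseline cases, 0.33 in others | 0.7 | 7% | 11% |

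At ρ = 0.3 the gain is about 2 points at 16.8–19.5% and about 0.5 at 8%. Against Fisher's exact test, which the plan also names and which would apply to such sparse tables, the stratified test is stronger at the low rates: about 12% against 6% at a frequency of 3%, and about 20% against 15% at 5% (ρ = 0.5).

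**A second parameterisation** with all 93 + 47 women, 16.8% baseline GAD, 70% persistence and 5% onset gives the same direction. At a risk ratio of 0.3, power is 60% (chi-square), 54% (Fisher) and 70% (stratified). At 0.5 it is 32%, 25% and 39%.

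**Chance imbalance.** The standard deviation of the baseline difference is √[p(1 − p)(1/80 + 1/40)]. At p = 0.168 this is √(0.1398 × 0.0375) ≈ 7.2 points. In simulation a difference above 10 points arises in about 15–18% of trials at 16.8–19.5%, but in about 1% at 5%. With no treatment effect and p of 16.8–19.5%, chi-square rejects in roughly 11–14% of those imbalanced trials at ρ = 0.5 and 18–22% at ρ = 0.7, against about 5% for the stratified test. Over all trials both tests stay at about 5% or below.

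**The case against.** The strongest reply is that nothing here is an error. An unadjusted comparison of randomised arms is valid. GAD supports the score outcomes, and the sample size makes no claim about it. This stands, and it limits the point to efficiency.

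A reader might infer from the 11–22% rejection rates that the planned test produces false positives. The documents do not support that. Those rates hold only within the minority of null trials that happen to be badly imbalanced, and the error averaged over all randomisations is controlled.

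The second reply is that a gain of 12–13 points takes favourable inputs, and this also stands. The 16.8–19.5% range describes anxiety in general, whereas the interview criterion is stricter and women on drug treatment for anxiety or depression are excluded. A risk ratio of 0.33 in every woman sits awkwardly with the look-back argument: if the 6-month window keeps baseline cases positive, the effect lies in new cases, the gain falls to about 4 points, and neither test has useful power. The overlap of windows has almost gone by T3, so it supports a high correlation only at the earlier visits.

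The reply that the stratified test loses power at 3–5% holds only against uncorrected chi-square. Against Fisher's test the stratified test still gains.

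A last reply is that adjustment may be specified in a fuller document. But section 2.8 states a method, so the point concerns a choice made and not a missing detail.

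**Conclusion.** The point holds as one of efficiency. The planned GAD comparison is valid but does not use a baseline diagnosis already in hand, and no named test of follow-up GAD uses both arm and baseline status. The gain over chi-square runs from about 2 to 13 points at a frequency of 16.8–19.5% with a uniform risk ratio of 0.33, through about 0.5–6 points at 8%, to nothing or a loss of up to about 5–6 points at 3–5%. It is about 4 points if only new cases respond. These sizes depend on GAD frequency, correlation, treatment effect and number analysed, none of which the protocol gives for GAD. The documents therefore do not support quoting a single large power loss, and they do not support calling the planned test biased. The change is worth making because it is cheap, and because fixing the adjustment in advance avoids choosing one after an imbalance has been seen.

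**What to change.** In section 2.8, make the main between-arm GAD analysis at each post-baseline visit a Mantel-Haenszel test stratified by baseline SCID GAD status, reported with a stratified risk difference and 95% CI. Prespecify an exact stratified version, and the event count below which it applies. Keep the raw frequencies by arm. State that Cochran's Q and McNemar's test are within-arm descriptions that do not support a treatment effect.

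The cost is a wording change and one layered cross-tabulation per visit, with no new data, visits or staff. The downside is slightly more analysis work, and little or no gain if interview-diagnosed GAD proves rare. The power of the exact stratified version was not simulated; like Fisher's test, it is likely to be conservative.

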## 3. Intervention

### 3.1. Rationale

The intervention was based on the principles of cognitive–behavioral therapy (CBT) and transdiagnostic treatments for emotional problems and includes three sections that address the main components of CBT: thoughts, pleasant activities and social contacts. CBT is one of the interventions that has obtained the best results for the treatment and prevention of perinatal anxiety [7,52,53]. On the other hand, transdiagnostic interventions may be more beneficial than specific interventions for each disorder, as scientific evidence suggests [7,37]. The need to develop this perinatal anxiety prevention program aimed at pregnant women is justified by the high prevalence of anxiety in the perinatal stage, as well as its possible consequences for both the mother and the baby [8,54]. Furthermore, there is a high comorbidity between symptoms of perinatal depression and anxiety [6], which indicates the importance of having a transdiagnostic intervention. Another aspect that highlights the need for a program of this type is the scarcity of existing psychological interventions to treat anxiety during pregnancy and postpartum [8,55]. A prevention program has been chosen because it would allow anxiety to be treated before it becomes a problem for the mother and her baby and would prevent future suffering [26]. Specifically, it would be a universal prevention program intended for all pregnant women regardless of whether or not they are at risk of anxiety. These programs have the advantage of increasing awareness about perinatal mental health as they provide information about its prevalence and risk factors, as well as tools to cope with emotional distress and increase the support network.

A CBT prevention program has been selected for development because it is found to obtain some of the best results in clinical practice [7,24]. The techniques included in the program, such as cognitive restructuring, behavioral activation or social support, have been selected because they repeatedly appear in the reviewed interventions that have shown greater effectiveness [7,8,24,32]. It should be noted that the intervention will not exclusively address anxiety, but also depression, due to the high comorbidity they present [6].

Regarding the method of application, it will be carried out at a group level, because group interventions obtain good results and involve lower costs, high satisfaction for users and high rates of compliance with the program [24]. Likewise, an electronically developed intervention has been chosen due to the benefits that this type of modality provides, such as lower cost and more convenience [31]. To ensure a safe and comfortable environment for the group participants, in the first session, some basic rules will be established for the proper functioning of the group. The therapy will be carried out by a psychologist via videoconference, which will reduce the disadvantages of online interventions, such as there being no interaction between the therapist and the patient or not attending to the needs that may arise during it [32].

To date, in Spain, we do not have any specific intervention protocol to address anxiety in pregnancy. We consider that it could help reduce its prevalence and the possible consequences it has on mothers and children, as well as promote the psychological well-being of women during pregnancy and postpartum. At the same time, being a transdiagnostic intervention, it would also allow comorbid depression symptoms to be treated.

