## Abstract

**Background:** Anxiety is one of the most frequent disorders during the perinatal stage that is associated with adverse health effects in women and their babies. In spite of this, preventive interventions during this stage are scarce. A long-distance intervention carried out during pregnancy can be an effective and accessible resource to help improve women’s emotional state. The objective of this study is to present and assess the effectiveness of a telepsychology cognitive–behavioral preventive intervention during pregnancy to manage anxiety. **Methods:** A random clinical trial will be carried out among pregnant women in Spain. The psychological intervention will take place via videoconference in seven weekly sessions, lasting one hour each, with groups of 6–8 pregnant women. Study outcomes will be collected via online questionnaires at five points in time: pre-intervention (baseline: t0), post-intervention (baseline: t1), follow-up at 1 month (t2), follow-up at 3 months (t3) and follow-up at 6 months (t4). The control group will receive usual pregnancy care (attendance at pregnancy follow-up consultations and information and answers to frequently asked questions provided by the midwife). Our primary hypothesis is that the intervention will decrease the frequency of women who present anxious symptomatology during pregnancy. The second objective is to analyze the effectiveness of this intervention to prevent depressive symptomatology during pregnancy, as well as postpartum anxiety and depressive symptomatology. The primary outcome measure is the difference in the mean anxiety score between the intervention and control groups assessed by the Edinburgh Depression Scale-Anxiety Subscale (EDS-3A), the State–Trait Anxiety Inventory (STAI) and Generalized Anxiety Disorder Screener (GAD-7) at the end of the intervention and at 1, 3 and 6 months postpartum. Generalized anxiety disorder (GAD) will be evaluated with the SCID clinical interview at the same time points. The secondary outcome will be determined by using the EPDS at the same time points. **Conclusions:** The results will determine whether a cognitive behavioral therapy applied via videoconference is well accepted by pregnant women, and if it is effective in preventing anxiety and emotional symptoms during the perinatal stage. If this intervention is an effective and useful resource among pregnant women, it can be implemented as a tool in Spanish healthcare.

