### 2.7. Sample Size

Power calculations were conducted to determine the minimum sample size. As there was no research describing the efficacy of CBT delivered via videoconference in this population, power calculations were based on published RCTs of unguided CBT for antenatal depression [38]. To detect a between-group effect corresponding to Cohen’s d of 0.55, the minimum sample size for each group (α = 0.05, 80% power) was 53 participants. Therefore, we aimed to recruit a minimum sample of 140 participants to allow for expected attrition.

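### The intervention is given in therapy groups of 6–8 women, but the sample size (2.7) and the named tests (2.8) make no allowance for correlation within a therapy group

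*Protocol article*

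**What the plan says.** - **Delivery.** The Abstract describes the intervention as given "in seven weekly sessions, lasting one hour each, with groups of 6–8 pregnant women". Section 3.1 confirms that "it will be carried out at a group level, because group interventions obtain good results" and adds that "The therapy will be carried out by a psychologist via videoconference". The session descriptions in section 3.2 rely on interaction, with debates and joint discussion of myths and vignettes.
- **Allocation.** Section 2.2 randomises individual women 2:1 in blocks. The control arm receives usual care. Section 2.1 counts group prenatal classes as part of usual care and gives no class size; the Abstract and the Introduction describe usual care without them.
- **Sample size.** Section 2.7 states: "To detect a between-group effect corresponding to Cohen’s d of 0.55", "the minimum sample size for each group (α = 0.05, 80% power) was 53 participants". The inputs come from trials of unguided CBT for antenatal depression. The recruitment target is 140, to cover attrition.
- **Analysis.** Section 2.8 says that "Variance analyses for repeated measurements will be performed" for the questionnaire scores, with Bonferroni comparisons. GAD diagnoses are compared by chi-square and Fisher's exact test, with Cochran's Q and McNemar's test across time. No therapy-group term, clustered variance or ICC appears.

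**The concern.** Women who share seven interactive sessions may end up with more similar anxiety scores than women in different groups. The trial is then partially nested: clustering arises in the intervention arm after individual randomisation. A test that ignores it takes the intervention mean to be more precisely estimated than it is. For any positive correlation the error runs one way, towards declaring the programme effective, and the Abstract names use in Spanish healthcare as the next step. Cochran's Q and McNemar's test deal with repeated measurements on one woman, not with correlation between women in a group.

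This goes beyond a detail left for later. The article gives a finished sample size and names its tests, and both rest on independence. The source of the power inputs would not have brought a clustering allowance with it, because the Introduction describes unguided programmes as used alone.

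**Working it through.** **Inputs from the protocol article:** d = 0.55, α = 0.05, 80% power, 53 per group and 140 recruited (2.7); 2:1 allocation (2.2); 6–8 women per group (Abstract).

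**Assumptions:** a two-sided test; m = 7 women per therapy group throughout; unclustered controls; ICC 0.02, 0.05 or 0.10, since the documents give none.

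**Step 1. Reproduce the stated figure.** A two-sided, two-sample t-test with equal arms, d = 0.55, α = 0.05 and 80% power needs 52.87 per group, which rounds up to 53. The match is exact, so the 53 contains no design effect.

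**Step 2. Arm sizes.** 140 split 2:1 is 93:47, and 93/7 ≈ 13 therapy groups. The stated minimum of 2 × 53 = 106 implies attrition of 1 − 106/140 = 24.3%; 106 completers split 2:1 is 71:35.

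**Step 3. Formulas.**
- Design effect, intervention arm only: DE = 1 + (m − 1) × ICC = 1 + 6 × ICC = 1.12 / 1.30 / 1.60.
- True SE in SD units: √(DE/n_int + 1/n_ctrl). Naive SE: the same with DE = 1.
- Ratio R = true SE / naive SE.
- Actual type I error of the naive test: 2 × [1 − Φ(1.96/R)].
- Power: two-sided t-test with noncentrality 0.55 / true SE and n_int/DE + n_ctrl − 2 degrees of freedom.

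Example at 93:47, ICC 0.05: naive SE = √(1/93 + 1/47) = 0.179; true SE = √(1.30/93 + 1/47) = 0.188; R = 1.049; type I error = 2 × [1 − Φ(1.96/1.049)] = 6.2%.

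**Step 4. Results.**

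| Women (int:ctrl) | ICC | R | Type I error of naive test | Power for d = 0.55 |
|---|---|---|---|---|
| 53:53 (stated) | 0 | 1.00 | 5.0% | 80% |
| | 0.02 | 1.03 | 5.7% | 78% |
| | 0.05 | 1.07 | 6.8% | 74% |
| | 0.10 | 1.14 | 8.6% | 69% |
| 93:47 (all 140 retained) | 0 | 1.00 | 5.0% | 86% |
| | 0.02 | 1.02 | 5.5% | 85% |
| | 0.05 | 1.05 | 6.2% | 83% |
| | 0.10 | 1.10 | 7.4% | 79% (80% by normal approximation) |
| 71:35 (106 completers) | 0 | 1.00 | 5.0% | 75% |
| | 0.02 | 1.02 | 5.5% | 73% |
| | 0.05 | 1.05 | 6.2% | 71% |
| | 0.10 | 1.09 | 7.3% | 67% |

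Basing the degrees of freedom on the small number of therapy groups lowers the clustered power by roughly one to four further points.

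**Step 5. Separate the causes.** At 71:35 power is already 75% with no clustering. That drop from 80% comes from applying a 1:1 calculation to a 2:1 allocation. Clustering takes a further 2, 4 and 8 points at the three ICC values.

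**The case against.** **The size depends on a figure the documents do not give.** Women are randomised individually, the curriculum is fixed, and the programme is universal prevention with follow-up to six months, so a low ICC cannot be excluded. At ICC 0.02 type I error rises by only about half a point at the planned 2:1 sizes. This stands: the omission is certain, its consequence is conditional.

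**A reader might infer that clustering leaves the trial underpowered.** The documents do not support that as a general statement. With all 140 women retained, power is about 80% or more up to an ICC of about 0.10. At 71:35 the first five points are lost to the allocation ratio.

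**A reader might infer that controls are plainly ungrouped.** Section 2.1 includes group prenatal classes in usual care. With no class sizes given, and the classes absent from other descriptions of usual care, treating controls as independent is an assumption that must be stated.

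**A reader might infer that the therapist adds to the correlation.** Sections 2.5 and 3.1 refer to one psychologist. If one person leads every group, any therapist effect is common to the whole arm and adds nothing to the correlation within groups relative to between them. The case rests on the interaction within groups.

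**Group effects can be left to an analysis plan.** This has some force for modelling detail. It has less force here, because a later plan would have to replace the tests named in 2.8 and qualify the figure in 2.7.

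**Conclusion.** The point holds in a moderate, conditional form. Delivery in interactive groups of 6–8 is fixed by the protocol, while the sample size and the between-arm tests assume independent women. If the within-group correlation is positive, the named tests understate the standard error and reject too often. Over an assumed ICC of 0.02 to 0.10 with 7 women per group, type I error is about 5.5% to 7.4% at the planned 2:1 sizes. Power falls from 80% to between 78% and 69% at the stated 53:53, and from 86% to between 85% and 79–80% at 93:47. Clustering by itself therefore undercuts the stated 80% at 53:53, but not clearly at full retention until the ICC reaches about 0.10. Attrition that shrinks the groups below 7 would reduce these effects. The correction should be made: it is cheap now, and it may be impossible later if group membership is not recorded.

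**What to change.** 1. Record the therapy-group number for every woman in the intervention arm.
2. In section 2.8, replace the repeated-measures ANOVA with a linear mixed model for repeated measures. Give it a random therapy-group effect in the intervention arm only (each control as her own cluster), a separate residual variance per arm, and Satterthwaite degrees of freedom.
3. Compare GAD frequencies between arms with standard errors clustered on therapy group, using a small-sample correction because there will be only about 13 groups.
4. State that controls are taken as unclustered, and reconcile this with the group prenatal classes in section 2.1.
5. In section 2.7, restate the power for the planned allocation over an assumed ICC range. This does not require enrolling more women.

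**Cost:** one extra variable, slightly wider intervals, a slightly lower stated power, and a change to the named primary analysis method, which is more than a rewording.
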